## Discussion

Kidney failure disease burden on patients and health care systems is considerable [19] and projected to increase in coming years [20]. Therefore, future increases in patient numbers and dwindling healthcare personnel due to the demographic change could be expected [21]. The landscape of dialysis care in Germany must change fundamentally to overcome these hardships. Innovative strategies such as SKIP-SH are positioned to play a pivotal role in realising these changes, provided they stand on solid scientific footing, which the SKIP-SH cohort study intends to provide.

A comprehensive dataset will be amassed within the study framework, encompassing a spectrum of clinical parameters. This multifaceted dataset will hold significant potential for addressing important scientific questions, thereby contributing substantively to advancing knowledge in the field. We particularly aim to elucidate and address three major issues.

First, the current global dialysis care landscape is characterised by a notable deficiency in home-based approaches [22]. Despite the potential advantages of home dialysis, including improved patient autonomy and quality of life, its prevalence remains disproportionally low [23–25]. Prevailing healthcare infrastructures often favour in-centre HD, perpetuating a systemic preference for facility-based care. In the context of this investigation, our objective is to clarify the factors underlying this phenomenon. Crossing demographic data and housing situations with clinical parameters will allow delving into the potential influence of living conditions on the choice of dialysis modality and treatment adherence, outcomes, and overall patient health after choosing one dialysis modality over another.

Second, clinical trials and day-to-day clinical care often tend toward a disease-oriented paradigm that focuses on pathological aspects rather than a goal-oriented or patient-centred approach. In dialysis care, this tendency might inadvertently result in therapy decisions intransigently prioritising longer life expectancy over quality of life and patients’ personal aspirations. This is especially true for elderly patients and those with multiple comorbidities [26, 27]. Furthermore, clinical course data present an opportunity to delve into the trajectory of disease progression, allowing the discernment of patterns, identification of critical milestones, and assessment of outcomes of certain treatments or interventions. This information is pivotal for refining treatment strategies and optimising patient care. Quality of life assessments provide insights into the holistic impact of dialysis on patients' well-being. By correlating these measures with clinical and demographic data, we could explore the determinants of enhanced quality of life, thereby guiding interventions aimed at improving patient-centred care. This analysis will be conducted on patients and their caregivers. Family caregivers play a pivotal role in treatment outcomes [28, 29]. They also tend to face hardships, which might lead to poor therapy adherence and efficacy [30, 31].

Third, the ongoing demographic change is expected to hit Germany particularly hard over the next decade [32, 33]. With the imminent challenge of more patients and fewer personnel, the incentive to enhance efficiency in healthcare delivery systems becomes paramount [34–36]. It is generally understood that PD at home is more cost-effective than in-centre HD and requires modest personnel input [6, 37]. This necessitates a proactive reassessment of our approach to resource allocation and treatment modalities. Assessment of the working hours required by medical personnel as part of our study will facilitate an evaluation of healthcare system demands and resource utilisation. This information is crucial for optimising staffing levels and improving the efficiency of healthcare delivery, both needed to address the emerging problems affecting dialysis provision in Germany.

Finally, biomaterials collection and subsequent analyses could be put into the context of clinical and laboratory data. This will provide the basis for a deeper understanding of underlying disease mechanisms and could potentially identify specific biomarkers and therapeutic targets in our patient population. This will also enable further research with a translational focus on problems relevant to PD, including peritoneal changes over time or systemic inflammation in the context of cardiovascular complications, aiding the development of future personalised therapeutic approaches [38, 39].

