Unfortunately, PD cannot be performed indefinitely. During the course of PD therapy, patients develop increasing peritoneal fibrosis and inflammation [10, 11]. These processes lead to detrimental changes in peritoneal transport properties and ultimately to technical failure of the procedure, typically after approximately five years, although prospective studies on this matter are scarce [12, 13]. In the worst case, a potentially fatal condition known as “encapsulating peritoneal sclerosis” develops [14, 15]. The condition shows great variability in between different countries, but in recent years there has been a decline in the incidence. This decline has been attributed to newly developed PD solutions and treatment strategies [16, 17]. Demonstrating the capability to influence one of the most feared complications of PD shows the immense potential and need for future translational research in this area.

Currently, high structural barriers restrict the further spread of PD. There is a lack of established treatment pathways and the necessary technical expertise due to the low prevalence of PD in many places. To address this problem, we launched *The Intersectoral Coordination Unit for the Sustainable Intensification of Peritoneal Dialysis in Schleswig–Holstein* (SKIP-SH) project at our clinic (Fig. 1). SKIP-SH constitutes a comprehensive initiative designed to augment the prevalence of PD among patients in the region. At its core, this project entails the establishment of a pre-dialysis coordination office to optimise shared decision-making with patients towards the most appropriate dialysis modality and mitigate existing institutional barriers that impede PD adoption. Additionally, SKIP-SH aims to create a training and education structure for patients and medical staff, creating a robust framework for sustainable PD implementation in Schleswig–Holstein. The SKIP-SH cohort study presented here aims to follow the SKIP-SH project and provide data-based proof for the assumed benefits of increased PD use.

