## Methods/Design

### Study aims and design

The SKIP-SH cohort study was designed as an accompanying prospective registry study to the clinical SKIP-SH project, which aims to sustainably strengthen PD use in Schleswig–Holstein.

This study aims to determine whether the theoretical benefits of PD are evident in practice and encourage translational research on PD. To do so, we have defined primary and secondary objectives as listed in Table 1.

**Table 1 Tab1:** Study objectives

Primary objectives	Secondary objectives
Documentation of clinical course, complications, and time on therapy of new dialysis patients	Identification of factors influencing good or poor disease-related quality of life of PD patients
Documentation of the reasons for choosing the treatment modality and the circumstances at the start of dialysis	Identification of factors influencing occurrence of clinical complications and dropout from therapy in PD patients
Documentation of quality of life of patients with CKD starting dialysis and their caregivers before, during, and after dialysis treatment initiation	Estimation of the ‘ecological footprint’ of PD patients
Establishment of a biomaterial bank of patients with CKD starting dialysis	Estimation of health care costs and labour time required to start and maintain PD therapy

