### Participant characteristics and inclusion and exclusion criteria

All patients presenting at our pre-dialysis coordination office with CKD stage 4 or 5 (estimated glomerular filtration rate < 30 mL/min/1.73 m^2^ for at least three months)[18] and their family caregiver (living in the same household) are eligible for inclusion in the study. Family caregivers will only undergo the quality-of-life assessment part of the study. All the inclusion and exclusion criteria are summarised in Table 2.

**Table 2 Tab2:** Inclusion and exclusion criteria

Inclusion criteria	Exclusion criterion
Patients with CKD stage 4 or 5	Inability to give informed consent
Family caregiver of a patient with advanced CKD	
Age ≥ 18 years	

Recruitment started on 1 December 2023 and is scheduled to run for three years; the follow-up will continue at least until 30 November 2028.

In line with the trend of patient numbers that we provided with a permanent dialysis access at our centre annually in recent years, we estimate that ~ 100 eligible patients with CKD qualifying for potential inclusion in the study will present to our pre-dialysis coordination office every year. We expect that the majority of these patients will start a dialysis procedure during the observation period. Patients will be followed up regardless of the dialysis modality they will eventually choose (PD or HD). We expect to include half as many family caregivers as patients.

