#### Data and materials to be collected

The collected dataset will include demographic parameters, clinical trajectory data, laboratory values, biomaterials, quality-of-life assessments, housing conditions, and essential working hours for medical personnel (Table 3).

**Table 3 Tab3:** Specific data to be collected

**Category**	**Detailed data**
Demographic data	Age; sex; marital status; ethnicity; weight; height; housing details (number of persons in the household, living space in square meters, rent/ownership); care level (if applicable)
Medical history	Comorbidities; current medication use; circumstances of and preparation for starting of dialysis; current dialysis regimen (including number of weekly sessions, Kt/V, dialysate composition and volume, incremental dialysis regimens, if applicable); residual urine excretion (if applicable); reasons for choice of dialysis type (personal preference/medical indications)
Clinical course	Number, duration, and reason for hospital admissions since start of dialysis/in the last year/since the last visit; frequency of outpatient medical consultations and laboratory checks; complications associated with the dialysis procedure; cardiovascular complications; need for care/increase of care level; date and cause of death (if applicable)
Estimated working time of medical staff in association with dialysis treatment	Duration of medical and nursing consultations; time required for learning the dialysis procedure
Laboratory data (as available from routine healthcare)	Blood count; electrolytes; clinical chemistry; lipid status; urinalysis
Quality of life	‘Kidney Disease Quality of Life 36-Item Short Form Survey (KDQOL-36)’ for patients and ‘Burden Scale for Family Caregivers (BSFC)’ for family caregivers
Biomaterials	Whole blood (15 mL per timepoint) and overnight peritoneal effluent

Only basic demographic data and quality of life will be collected from family caregivers; the remaining items will be collected only from the patients.

Table 4 delineates the designated time points for study visits and data/biomaterial collection. Study visits that do not require sampling of biomaterials may be completed via remote communication.

**Table 4 Tab4:** Data acquisition time points

Time point	First presentation (V0)	Start of dialysis/change of dialysis modality^a^ (V1)	+ 3 months^a, b^ (V1.2)	+ 6 months^a, b^ (V1.3)	+ 12 months (V2)	Annually thereafter (V3, V4, V5, etc.)
Demographic data	x					
Medical history	x	x	x	x	x	x

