Clinical course	x	x	x	x	x	x
Estimated working time		x	x	x	x	x
Laboratory data	x	x	x	x	x	x
Quality of life	x	x	x	x	x	x
Biomaterials	x	x			x	x

^a^If the first presentation takes place after the start of dialysis and no change in dialysis type occurs, visits V1-V1.3 will be skipped

^b^May be completed via remote communication

The biomaterials obtained will include blood samples and overnight PD effluent. Samples will be stored to allow for analyses of the transcriptome, DNA(-methylation)-profiling, immunophenotyping of blood leukocytes and cells in the PD effluent, as well as analyses of serum and plasma markers, and soluble markers in the PD effluent.

Digital data documentation and biomaterial storage will be pseudonymised; only the study investigators will have access to the information that enables re-identification.

While data and biomaterials will be stored indefinitely, study participants can revoke their consent at any time and may request the deletion of their data and disposal of their biomaterials.

The publication and provision of data or biomaterials to third parties for scientific purposes will be done exclusively in an anonymised manner.

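### The Discussion aims to explain low home-dialysis use, but the cohort can only describe modality choice among patients who reach the coordination office

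*Protocol article*

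**What the plan says.** The first major issue in the Discussion is the scarcity of home-based dialysis. The article gives a system-level account of it, "Prevailing healthcare infrastructures often favour in-centre HD, perpetuating a systemic preference for facility-based care", and follows with the aim: "In the context of this investigation, our objective is to clarify the factors underlying this phenomenon". The Background likewise points to structural barriers, namely missing treatment pathways and missing expertise.

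The section on participant characteristics defines who can enter: "All patients presenting at our pre-dialysis coordination office with CKD stage 4 or 5", together with a caregiver from the same household. According to the Background, that office is meant to support shared decision-making and to "mitigate existing institutional barriers that impede PD adoption".

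Table 1 lists as a primary objective "Documentation of the reasons for choosing the treatment modality and the circumstances at the start of dialysis". Table 3 collects, under medical history, "circumstances of and preparation for starting of dialysis" and also "reasons for choice of dialysis type (personal preference/medical indications"). Footnote a to Table 4 provides for late entry: "If the first presentation takes place after the start of dialysis and no change in dialysis type occurs, visits V1-V1.3 will be skipped".

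**The concern.** The aim concerns a phenomenon in the whole dialysis population, and the article itself places part of its cause in the health-care system. The sample is drawn after a step at which that cause may already have acted. A patient whose physician never considers PD, or never refers, does not enter the study.

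If the aim stays as worded, factors that vary among counselled attendees, such as housing, preference and comorbidity, could be reported as the reasons why PD is rare. They would be the reasons for choosing one modality over the other once a patient has reached a service built to make PD accessible. Those are different questions, and they point to different remedies in policy: patient counselling on one side, referral and provision on the other.

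**Working it through.** The article gives no figure to reproduce on this point. The check compares the aim with the sampling frame and the data items.

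**Step 1. Who is observed.**

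| Group | In the cohort? | Basis |
|---|---|---|
| Presents before dialysis, planned start | Yes | Eligibility text |
| Presents before dialysis, later starts urgently | Yes | Follow-up does not depend on the modality chosen |
| Starts dialysis first, presents afterwards | Yes, from V0; V1 to V1.3 skipped unless the type changes | Table 4, footnote a |
| Never presents at the office | No | Eligibility text |

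Medical history, which holds the start circumstances, is scheduled from V0 onward. The third group can therefore still supply that item.

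**Step 2. What the fourth group takes away.** Let *b* be the share of dialysis starters in the region who never present. Let *u_A* and *u_N* be the proportions of unplanned starts among those who do and do not present. The regional proportion is

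*u* = (1 − *b*) × *u_A* + *b* × *u_N*.

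At best the cohort estimates *u_A*. As *u_N* can lie anywhere from 0 to 1, *u* lies between (1 − *b*) × *u_A* and (1 − *b*) × *u_A* + *b*, an interval of width *b*. The same holds for the PD share. The article gives no value for *b*.

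**Step 3. Sample size does not help.** About 100 eligible patients a year over three years of recruitment gives 100 × 3 = 300 presenting. More attendees make *u_A* more precise and leave *b* and *u_N* unknown. The effect of non-referral on modality is a contrast between presenters and non-presenters, and one side of it has no data.

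**Step 4. The analysis cannot recover it.** The comparisons in the Statistical analysis section (PD against HD, regression on patient characteristics, time-to-event models) are all made within the cohort. Adjustment within the cohort cannot supply patients who are outside it.

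**Step 5. The reasons item.** The two categories named in Table 3 are personal preference and medical indications. No organisational reason is named, such as PD not offered, PD not available or late referral. Such reasons could occur among attendees, but the item as printed has no named place for them.

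**The case against.** The strongest reply is that the study's formal aims are more modest. Table 1 asks for documentation of reasons and circumstances, which can be met among attendees. The quoted aim stands in the Discussion, and the sentence after it narrows the work to living conditions, modality choice and outcomes, which the cohort can address. The 4.3% PD share in Schleswig–Holstein is given as background, no regional extrapolation is announced, and the analyses are called exploratory. All of this stands, and it limits the weight of the point. It does not remove the mismatch, because living conditions are not the systemic factors that the preceding sentences put forward.

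Three stronger readings are tempting, and the article does not support them:

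- A reader might infer that unplanned starts cannot appear at all. Footnote a to Table 4, the start-circumstances item and follow-up regardless of modality show that they can.
- A reader might infer that the three-month eGFR criterion shuts out patients who arrive in kidney failure without earlier values. It is a chronicity criterion, and nothing says that the three months must precede dialysis.
- A reader might infer that institutional barriers are absent among attendees, so that only patient-level factors can vary. The office is meant to reduce barriers, outpatient physicians still treat these patients, and late referral or poor preparation can differ between attendees. Only complete non-referral is unobservable.

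It can also be said that counts from one centre's access records do not cure the problem. That is right: they miss other centres and starts without a permanent access. They are useful only as a partial denominator.

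Finally, the two categories in the reasons item may be examples, and the full data form may already hold more. In that case the second change below is only a check.

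**Conclusion.** The point holds in a limited form. The cohort can describe modality choice and start circumstances among patients who reach the coordination office, including late-referred and unplanned starters who get there. It cannot estimate non-referral as a cause of low PD use or the regional share of unplanned starts, and the wording of the reasons item leans further towards patient-level explanations.

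The size is not computable from the article: the unidentified range for a regional proportion equals the share of starters who bypass the office, and that share is not given. The conclusion rests on the eligibility text being the only route into the study and on no outside comparison source being used; the article describes none. It affects what may be concluded from the study and leaves the documentary objectives intact.

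**What to change.** 1. Restate the aim in the Discussion, and any conclusion drawn from it, as factors for modality choice among patients seen at the coordination office.
2. Add organisational reasons to the reasons item in Table 3: PD not offered, PD not available, late referral. Medical history is scheduled at every visit, so patients already enrolled can be updated at the next one.
3. In the annual interim reports, give aggregate counts from the centre's own permanent-access records, a source the article already draws on for its patient estimate. Split them by PD/HD and planned/unplanned and, for the study years, by seen or not seen by the office. Label them as a partial denominator that omits other centres and starts without a permanent access.

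The cost is a narrower claim, a small change to one data item and a short yearly extraction. Eligibility and the visit schedule stay as they are. The third change assumes that the access records allow a start to be classed as planned or unplanned; where they do not, that split should be reported as unknown.

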## Data Availability

Data and biomaterials will be shared with researchers who provide a methodically sound proposal. Individual deidentified data collected during the trial will be made accessible. Proposals should be directed to the corresponding author. Data requestors must sign a data access agreement to gain access. Data will be shared to achieve the aims in the approved proposal.

## Abbreviations

CKD: Chronic kidney disease
HD: Haemodialysis
KRT: Kidney replacement therapy
PD: Peritoneal dialysis
SKIP-SH: Intersectoral Coordination Unit for the Sustainable Intensification of Peritoneal Dialysis in Schleswig-Holstein;* Sektorenübergreifende Koordinierungsstelle zur nachhaltigen Intensivierung der Peritonealdialyse in Schleswig-Holstein* [in German]
